# Promoting physical activity through supervised vs motivational behavior change interventions in breast cancer survivors on aromatase inhibitors (PAC-WOMAN): protocol for a 3-arm pragmatic randomized controlled trial

**DOI:** 10.1186/s12885-023-11137-1

**Published:** 2023-07-05

**Keywords:** Survivorship, Aromatase inhibitors, Quality of life, Physical sctivity, Active lifestyle, Lasting behavior change, Self-determination theory

## Abstract

**Background:**

Aromatase inhibitors (AI) are frequently used to treat hormone-receptor-positive breast cancer, but they have multiple adverse effects (e.g., osteoporosis, arthralgia), resulting in premature therapy discontinuation/switch. Physical activity (PA) can attenuate these negative effects and improve quality of life (QoL). However, most cancer survivors fail to perform/sustain adequate PA levels, especially in the long-term. Theory-based interventions, using evidence-based behavior change techniques, aimed at promoting long-term behavior change in breast cancer survivors are effective, but remain scarce and fail to promote self-regulatory skills and better-quality motivations associated with sustained PA adoption. This paper describes the design of the PAC-WOMAN trial, which will test the long-term effectiveness and cost-effectiveness of two state of the art, group-based interventions encouraging sustained changes in PA, sedentary behavior, and QoL. Additional aims include examining the impact of both interventions on secondary outcomes (e.g., body composition, physical function), and key moderators/mediators of short and long-term changes in primary outcomes.

**Methods:**

A 3-arm pragmatic randomized controlled trial, involving a 4-month intervention and a 12-month follow-up, will be implemented, in a real exercise setting, to compare: 1) brief PA counseling/motivational intervention; 2) structured exercise program vs. waiting-list control group. Study recruitment goal is 122 hormone-receptor-positive breast cancer survivors (stage I-III), on AI therapy (post-primary treatment completion) ≥ 1 month, ECOG 0–1. Outcome measures will be obtained at baseline, 4 months (i.e., post-intervention), 10 and 16 months. Process evaluation, analyzing implementation determinants, will also be conducted.

**Discussion:**

PAC-WOMAN is expected to have a relevant impact on participants PA and QoL and provide insights for the improvement of interventions designed to promote sustained adherence to active lifestyle behaviors, facilitating its translation to community settings.

**Trial registration:**

April 20, 2023 – NCT05860621.

April 21, 2023 – https://doi.org/10.17605/OSF.IO/ZAQ9N

April 27, 2023 – UMIN000050945.

**Supplementary Information:**

The online version contains supplementary material available at 10.1186/s12885-023-11137-1.

## Background and rationale

Cancer is expected to become the leading cause of death and the single most important barrier to increasing life expectancy all over the world in the present century [1]. Still, the large increase in cancer survival rates, derived from advances in cancer detection and treatment, brought new challenges to cancer management and care [1]. Survivorship (i.e., from diagnosis to the end of life) is often related with long-term treatment side effects (e.g., fatigue), increased risk of cancer recurrence, and higher vulnerability to chronic diseases; all of which adversely affect cancer survivors’ quality of life (QoL) [2]. Hence, continuous care services need to be provided even long after the active treatment, placing increasing pressure on health care systems (USA costs estimated to be over US$450 billion in 2030) [3].

Breast cancer is the second most common cancer in Portugal and one of the three most common worldwide [4]. Breast cancer survivors diagnosed within the past five years were estimated to be 6.8 million worldwide and 155.5 thousand in Portugal [1]. About 75% of breast cancer diagnoses are hormone-receptor-positive [5], and often treated with aromatase inhibitors (AI), after active treatment, in post-menopausal women [6]. AI improve disease-free survival by 10–40% [7], but have several adverse side effects (e.g., arthralgia, osteoporosis, menopausal symptoms) that affect QoL [8]. Body image is often compromised in breast cancer survivors, negatively affecting daily functioning and QoL [9]. These side effects often lead to premature AI discontinuation, and eventually, to lower treatment efficacy and increased mortality [10].

Physical activity (PA) is safe and should be an integral and continuous part of care for all individuals diagnosed with cancer [11]. There is compelling evidence suggesting that PA plays an important role in improving longevity among cancer survivors [12]. PA effectively ameliorates short- and long-term adverse effects of cancer therapies (e.g., comorbid conditions), improves physical fitness, physical functioning and sleep, attenuates cancer-related fatigue, enhances body image and QoL, and decreases cancer recurrence and mortality [12, 13]. PA also allows women to benefit from endocrine therapy while being protected against the related risk of osteoporosis, fracture, and ultimately cancer recurrence or death [14]. Thus, PA in breast cancer survivors, and specifically among women on AIs, is paramount to improve health outcomes, QoL, and prevent therapy discontinuation.

However, the health system is overburden, and it does not have an integrated solution (that incorporates exercise programs) for cancer survivors who finish the active treatment and often feel overwhelmed by the necessity of self-managing treatment side effects on their own [15]. Thus, most cancer survivors fail to meet established guidelines for PA [16], not benefiting from exercise positive effects on health and QoL. Global (lack of motivation), practical (affordability) and health-related exercise barriers (fatigue, pain) are often reported at the individual level [15], but also barriers concerning the implementation of PA programs in oncological populations [17]. Additionally, the existence of community exercise programs and their integration into health care is still scarce [18, 19]. Still, healthcare professionals can have a strong impact on cancer survivors’ PA adoption [20]. Also, providing PA assessment, brief counseling, and referral as part of routine healthcare has been recommended in the WHO Global Action Plan for Physical Activity 2018–2030 [21].

Theory-based interventions, using evidence-based behavior change techniques (e.g., self-monitoring, goal setting or action planning) known to mediate long-term PA adherence [22], are effective in breast cancer survivors [23], but still scarce [24]. Also, most interventions fail to provide validated self-regulatory tools or explore meaningful links between PA and patients’ values and life aspirations to foster lasting behavior changes [25]. Prior research has shown that internal (better quality) forms of motivation play an important role in PA and behavior sustainability [26, 27], suggesting that self-determination theory (SDT) [28] can be a valid framework to promote sustained adherence to PA. We have also started establishing SDT relevance in the design and delivery of PA interventions [29, 30], confirming that a need-supportive intervention climate enhances people’s wellbeing and their ability to self-regulate and sustain behavior changes [31]. Brief counseling interventions to foster PA, involving an approach to motivations, barriers, preferences, readiness, and patient's opportunities to perform PA [32], have gathered evidence of effectiveness, compatible with clinically relevant increases in PA levels, in the general population [33]. However, there is still a lack of studies assessing the external validity of this type of interventions, when implemented in real-world settings, which limits the generalizability of such results [34].

In sum, although regular PA is a promising and safe way of helping cancer survivors navigate their disease, thus also alleviating the growing pressure on the health care system, most cancer survivors do not meet the recommended PA doses. It is a goal of this project to overcome the abovementioned shortcomings, by testing an intervention model informed by solid evidence and a robust theoretical rationale [28], provided by qualified exercise professionals (i.e., with a master in Exercise Sciences) – with the potential to add value to the treatment process, improving the therapeutic effect and safety of the exercise practice [35].

### Objectives

This paper describes the protocol of a pragmatic randomized controlled trial (RCT), PAC-WOMAN, targeting Portuguese post-menopausal women diagnosed with hormone-receptor-positive breast cancer, currently on Aromatase Inhibitors. This project primary aims are:a) To develop and test the long-term (16-month) effectiveness and cost-effectiveness of two 4-month group-based interventions, compared to a control waiting list, on promoting sustained changes in PA, sedentary behavior, QoL, and healthcare services’ use (primary outcomes)b) To compare the effects of both interventions (i.e., brief PA counseling vs. structured exercise) on long-term changes in our primary outcomes, as well as their cost-effectivenessc) Evaluate pretreatment moderators of 4-month and 16-month changes in PA, sedentary behavior, and QoLd) Identify critical motivational (theoretical) mechanisms of change in PA, sedentary behavior, and QoL, and explore their mediating role.

As secondary aims, we will study the impact of both interventions on AI therapy continuation, adverse events of treatment, disease-free survival, body composition, sleep quality, physical parameters (e.g., muscular strength), and psychosocial factors (e.g., body image). Furthermore, process evaluation will also be conducted seeking to analyze implementation facilitators and barriers.

### Methods: Participants, interventions, and outcomes

This protocol follows SPIRIT guidelines [36]. The SPIRIT checklist can be found in Additional File 1.

#### Rationale for the PAC-WOMAN trial

Supervised exercise programs may provide significant symptomatic benefit for patients living with or beyond cancer [11, 12], however their widespread implementation may be restricted by lack of facilities and funding. Indeed, there is a lack of effective PA interventions that are low-cost and can be implemented at scale and fully-embedded in a system [37]. Furthermore, once these exercise programs end, the sustainability of PA behavior and its subsequent health outcomes may be at risk. Thus, there is a need for effective, scalable, low-cost interventions to enhance the adoption and maintenance of regular PA. Brief counseling interventions that promote autonomous motivation for free-living PA, reinforcing self-regulation resources, may be an alternative, less expensive, solution. Evidence has suggested that brief counseling interventions may be as effective as more intensive interventions [38].

Indeed, there is an urgent need for affordable and practical interventions that can be delivered in real-world health care or community settings and have similar degrees of effectiveness [34]. A systematic review exploring differences between supervised exercise, home‐based exercise, and walking advice for intermittent claudication has not found clear differences in quality of life or self‐reported functional impairment between supervised exercise and free-living PA solutions, suggesting that the latter might also be important alternatives within PA promotion [39]. In line with this, brief PA counseling interventions, that are underpinned by theoretical models of behavior change and incorporate behavior change techniques, such as identifying barriers, self-monitoring, goal setting, and feedback provision, have been shown to increase PA in the general population [40, 41], as well in people with physical disabilities [42].

In sum, existing interventions targeting supervised exercise, although very effective in promoting short-term health outcomes [43], may be labor intensive and costly for staff and participants. Also, long term effects, once the intervention is finished, may be jeopardized given that supervised interventions may have the detrimental effect of patients’ internalization of the message that their condition is to be dealt with by procedures and techniques essentially under the responsibility and “steering” of an external expert (e.g., simply follow an exercise prescription), thus promoting an external locus of causality. In contrast, theory-based, evidence-informed brief counseling, delivered in a manner that reduces dependence on staff and facilitates self-regulatory skills, could alleviate time and financial barriers while promoting free-living, integrated into daily-life, PA/exercise. From a self-determination theory (SDT) perspective [28], lasting behavior change does not depend on complying with external demands for change but rather on accepting the regulation of change as one’s own. This requires internalizing the regulation of relevant behaviors and integrating them with one’s sense of self and one’s values and goals, so they can become the basis of autonomous regulation [27].

Thus, the PAC-WOMAN trial will test effectiveness and cost-effectiveness of these 2 types of interventions (supervised structured exercise vs. brief theory-based PA counseling) against a waiting-list, standard care, control group. This is of importance given that although an improved health profile (e.g., lower blood pressure, lower body mass index, improved tumoral biomarkers, cardiorespiratory fitness, physical function) is expected as a short-term result of the exercise intervention, the maintenance of the PA/exercise habits after the end of the intervention remains to be determined (and consequently its long-term health outcomes). On the other hand, will a brief motivational (SDT-based) intervention (lighter in time and resources) be enough to trigger a more physically active lifestyle? And will the potential behavioral, motivational, and self-regulatory changes endure in the long term? (With a sufficient magnitude to produce positive health outcomes?).

This contrast can be better understood considering the theoretical background of SDT [28], a macro theory of human motivation widely used to develop health behavior change interventions in multiple health domains and populations [26, 27]. This framework was selected because it accounts for the nature and function of motivation [28] and provides a theoretical explanation for both behavioral and psychological health issues in symptomatic populations [44]; issues that represent critical priorities in cancer survivor care [45]. SDT proposes that creating a need-supportive environment, that fulfills one’s psychological needs for competence, autonomy, and relatedness, will foster greater levels of autonomous (self-determined) motivations (i.e., self-endorsed reasons to perform a behavior, coherent with one’s core values and interests), which will in turn lead to long lasting behavior change [28]. Systematic reviews and meta-analyses provide empirical support for the use of SDT to develop PA behavior change interventions for adults in general [26, 27]. In cancer populations, a few correlational studies have provided support for SDT propositions, namely for the role of autonomy support and autonomous motivations on PA adoption and psychological wellbeing [46–48]. Still, SDT-based interventions targeting cancer survivors are only giving the first steps. To date, we could only find a pilot intervention study testing the positive effects of an autonomy-supportive exercise instructing style on breast cancer survivors’ wellbeing [49] and a very recent protocol for another pilot SDT-based intervention to promote PA via videoconferencing technology in young adults [50].

#### Study design and setting

PAC-WOMAN is a three-arm, superiority parallel-group, pragmatic randomized controlled trial (RCT), comprising a 4-month intervention period and a 12-month follow-up, that will be conducted to evaluate the effectiveness of two interventions aimed at promoting active lifestyles and improved quality of life in the long-term, albeit with different approaches (brief PA counseling vs. supervised structured exercise), compared to a control group.

Clinical trials can be conceptualized across a continuum from explanatory to pragmatic, with the former assessing if a program could work under ideal circumstances and the latter determining if it could work in real world conditions. Pragmatic trials are necessary for developing and testing interventions using the settings, resources, patients, and approaches to which they will ultimately be implemented [51, 52], thus ensuring that research funds have the greatest potential to impact patient and population health and have therefore been recommended [53].

This project will be conducted under real world circumstances at a main urban center served by several hospitals. Interventions were designed to take place at local gyms, with facilitated accessibility and appropriate equipment and facilities. Recruitment of participants is taking place via dissemination of the trial in main hospitals with oncology centers. A schematic description of the study phases and participant’s timeline, according to SPIRIT, is presented in Table 1. Participants will be enrolled in cohorts or “waves”. Ethics approval was obtained prior to study development/implementation from the faculty responsible for the study (FEFD: M25C21) and all recruitment hospitals (CAML: 285/21; HFF: 10/2022; IPOLFG: UIC/1499; CHLO: 2281). The trial is being conducted in accordance to the declaration of Helsinki for human studies from the World Medical Association [54].

**Table 1 Tab1:**
[figure not shown]
SPIRIT diagram flow for the PAC-WOMAN study

Legend: *C1* Cohort 1, *C2* Cohort 2, *C3* Cohort 3

#### Participants

Recruitment (ongoing) will aim for 122 Portuguese breast cancer survivors who have completed primary cancer treatment and are currently under aromatase inhibitors therapy and will subsequently be randomized to receive the brief PA counseling (PAC), the structured exercise program (StEx), or to a waiting list control group.

The inclusion criteria for entering this study are: 1) post-menopausal women, below 70 years old; 2) histologically confirmed hormone-receptor-positive breast cancer (stage I, II, III); 3) having initiated AI hormonal therapy following the primary treatment (surgery, radiotherapy, chemotherapy, etc.), at least 1 month before being enrolled; and 4) ECOG-Performance Status 0–1 (being able to perform light-to-moderate physical activities). The exclusion criteria are: 1) evidence of stage IV cancer or synchronous tumors; 2) uncontrolled hypertension, cardiac or pulmonary disease; 3) contraindications to exercise training according to the assistant doctor; 4) inability to provide informed consent; and 5) expected inability to fulfill the proposed program schedule.

Given the study design, sample size estimations were calculated for primary outcomes having one-way factorial analysis of variance with repeated measures as the reference statistical analysis. Based on previous research findings, and considering a 25% dropout, the sample size was estimated in 98 participants to detect a small to moderate effect size (α = 0.05; statistical power = 0.80) using G*Power 3.1. Consensual criteria on sample size needs for mediator/moderator analyses are not consensual and depend on the procedure and number of indicators and pathways in the models; therefore, we increased the estimated number of participants in 25%, obtaining a final estimated sample size of 122 participants.

#### Recruitment and screening

Ongoing recruitment is taking place via study dissemination and referral from the medical teams of several main hospitals (Hospital de Santa Maria, Hospital [name] Fonseca, Instituto Português de Oncologia – Lisboa, Hospital de São Francisco Xavier, and CUF Tejo/Descobertas). A website (https://pac-woman.ulusofona.pt/) and a Facebook page (https://www.facebook.com/projeto.pacwoman) were created to disseminate the project and help with the recruitment and dissemination process. Informative brochures for physicians and patients were produced and delivered in recruiting hospitals.

The post-COVID-19 pandemic period of this study is expected to create additional difficulties to recruitment [55–58]. As a result, additional, more direct, strategies like contacting patient associations, circulating Facebook adds tailored to women in the study age range in special cancer group pages, requesting public figures that survived breast cancer to disseminate our study, distributing flyers directly to the target population in cancer-related sport events, or advertising our study in TV/Radio shows, are also being considered.

Patients referred by the medical teams are, then, contacted by phone by the research team to receive detailed information about the study. Alternatively, in case of preference, patients can also call the research team directly, or manifest interest via email or Facebook. In all cases, after confirming eligibility criteria and interest to participate, patients are asked to assist to an informational session and, in case of interest, sign the inform consent form. Participants are informed that they are under no obligation to participate and may withdraw their consent at any time. Additional consent provisions for collection or sharing of participant data are also obtained. A manual on recruitment and screening procedures was produced.

#### Randomization and blinding

After signing the informed consent and completing the baseline assessments, participants are randomly allocated to one of the three arms. Allocation is being made according to an automated computer-generated randomization scheme performed by a member of the research team not directly involved with participants. Adjustments in the allocation ratios might be made if recruitment takes longer than expected and interventions are required to start for timely reasons. Group assignment is only communicated to participants after all baseline testing is finished.

Participants and research team staff are unaware of group allocation at the time of recruitment and baseline assessments because randomization is only performed after participants have completed baseline assessments. This study will involve behavior change interventions, preventing any concealment of group allocation after randomization from either participants or intervention counsellors. Nonetheless, participants will be blinded to the study rationale. Also, to minimize bias, physical activity and sedentary behavior (primary outcomes) are objectively assessed using accelerometers and psychometric data are collected by self-report and introduced in the Qualtrics platform in its raw state. All outcome data will be kept blinded until the final data entry for the entire study is completed.

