#### Criteria for discontinuing or modifying allocated interventions

This is an adaptive, pragmatic trial, subject to real world conditions, thus adaptations may be needed. Data retrieved during trial implementation (mainly from process evaluations, via focus groups with participants at the end of each cohort and interviews with session facilitators, staff from recruiting hospitals and stakeholders) will help to decide the need to adjust aspects of the study as it continues (without undermining the validity and integrity of the trial) [61]. For instance, adjustments might be made in the order or interval between the sessions, based on participants' feedbacks; group allocation ratios might be adapted if recruitment takes longer than expected and, for timely purposes.

It is important to highlight that the PAC-WOMAN trial comprises two non-invasive interventions, with minimal risk of harm. Participants will go through a comprehensive assessment at baseline and those enrolling in the structured exercise program will be provided with a tailored, individualized, prescription, with a gradual progression, always adapted to their needs and capacities. Participants will be asked to report any adverse event and we will keep a close contact with the medical team, always assuring participants’ safety. Also, a personal accident insurance will be contracted and triggered whenever needed.

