#### Statistical methods

Factorial Anovas with repeated measures, adjusting for potential covariates (e.g., primary treatment, length of AI therapy), will be conducted for primary and secondary outcomes. The analysis will be intent-to-treat to include compliance effects in the overall assessment. Last Observation Carried Forward will be used to impute missing values. A per-protocol analysis will also be conducted without participants who do not attend at least 80% of the sessions. Normality plots and Kolmogorov–Smirnov tests will be used to test normality of outcome variables. If substantial departure from normality is found, square root log transformations will be computed. If normality is still not satisfied, non-parametric tests (e.g., Kruskal–Wallis) will be employed. As the experimental design is factorial, multiple comparison adjustments will not be appropriate.

Mediators of change, i.e., mechanisms by which participants change their lifestyle behaviors and QoL (vs. controls), will be explored using structural equation modeling (AMOS 18.0) and multiple mediation analysis (PROCESS macro v. 3.3 for SPSS). Putative candidates will include motivational (e.g., autonomous motivations) and self‐regulatory (e.g., action planning) variables. Mediation is said to occur when the causal effect of an independent variable (X) on a dependent variable (Y) is partially or fully explained by a mediator (M) [93]. Indirect effects will be tested using Preacher and Hayes’ procedures [94]. Bootstrapping with 5000 samples and 95% CI estimates for indirect effects will be calculated and assumed significant (α = 0.05) if the CI does not encompass zero [95, 96]. The ratio of the indirect effects to the total effects (P_*M*_) will be calculated to express the strength of the mediation effects [95]. Moderators, i.e., baseline characteristics that have an interactive effect with the intervention on the outcome(s), will be assessed to better understand individual differences in intervention effects [97, 98]. Moderation effects on primary outcomes will be conducted at intervention or follow-up’s end.

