#### Oversight and monitoring

##### Adverse event reporting and harms

All subjects will be followed up for adverse event collection, related and non-related to the intervention (when applicable), through self-reporting at the beginning of each session, and at each assessment point visit using a questionnaire specifically built for this study, based on the Common Terminology Criteria for Adverse Events (CTCAE v.5). In addition, between sessions or assessment visits, participants will be asked to contact the clinical team in case of difficulties.

The research team will meet regularly once a week to discuss participants and intervention progress, emerging challenges and required adjustments to the sessions. These meetings will also serve to monitor data on outcomes and adverse events, and to oversee participants’ safety. A data monitoring committee will not be needed for the PAC-WOMAN trial, given that both interventions are non-invasive with minimal risk of harm. In addition, participants will be protected by a personal accident insurance, activated whenever needed.

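### Allocation ratios may change during a trial that enrols in cohorts, and the stated model names no cohort term; if a ratio does change, arm comparisons will carry cohort differences in outcome change

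*Protocol article*

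**What the plan says.** Study design and setting: "Participants will be enrolled in cohorts or" waves. The legend of Table 1 names three cohorts.

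Randomization and blinding: participants are allocated to one of three arms by a computer-generated scheme run by a team member not directly involved with participants. No starting ratio is stated. Then: "Adjustments in the allocation ratios might be made if recruitment takes longer than expected and interventions are required to start for timely reasons".

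Criteria for discontinuing or modifying allocated interventions: the permission is repeated among the trial's adaptations, "group allocation ratios might be adapted if recruitment takes longer than expected". The section says adaptations must not undermine validity, but it does not say when within enrolment a ratio may change or on what information.

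Trial status: recruitment began in January 2022 and rates were very low. By 27 April 2023, 68 women had been randomized against a goal of 122, with completion expected in December 2023.

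Statistical methods: factorial repeated-measures ANOVAs, "adjusting for potential covariates (e.g., primary treatment, length of AI therapy" being the examples given. The Potential covariates section and Table 2 list demographic, medical, treatment and dietary factors. Cohort and calendar period appear in none of these places.

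On access to data, Randomization and blinding says "All outcome data will be kept blinded until the final data entry for the entire study is completed". Of the weekly team meetings, Adverse event reporting and harms says "These meetings will also serve to monitor data on outcomes and adverse events".

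**The concern.** Randomization protects the comparison of arms among people randomized under the same ratio. If the ratio differs between cohorts, each arm is a different blend of cohorts, and a pooled comparison that ignores cohort mixes the arm effect with whatever distinguishes the cohorts.

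The planned model contains baseline, so a stable difference in level between cohorts (for instance from a different recruitment route) cancels from the group-by-time effect. What does not cancel is a cohort difference in change. The schedule leaves room for one: assessments fall at 0, 4, 10 and 16 months, and no follow-up is a whole number of years after baseline. A seasonal pattern in activity would therefore enter the change score according to the month in which a cohort starts. Recovery of activity after the pandemic could also differ between a cohort starting in 2022 and one starting in late 2023.

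The condition attached to the permission, slow recruitment, appears to have been met already. The outcomes at stake are the primary ones, in a trial sized for a small to moderate effect.

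**Working it through.** The article gives no figure for this point, so there is none to reproduce. The calculation below rests on assumptions and shows their range.

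**Inputs from the article.** Target 122; 68 randomized by 27 April 2023; three cohorts; three arms.

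**Assumptions, not in the article.**
- Cohort sizes of 34, 34 and 54: the 68 split equally, and 122 − 68 = 54 still to come.
- A 1:1:1 ratio in the first two cohorts.
- No true treatment effect and no dropout.
- Mean outcome change in the last cohort differs from the others by δ = 0.3 to 0.5 SD, equally in all arms.

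**Formulas.**
- Bias = (last cohort's share of the intervention arm − its share of the control arm) × δ.
- SE = √(1/n₁ + 1/n₂), in SD units.
- Type I error = Φ(−1.96 − z) + Φ(−1.96 + z), with z = bias/SE.

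**Constant 1:1:1.** Each arm has 122/3 = 40.7, and the last cohort's share is 54/122 = 44.3% in every arm. The bias is 0 and the type I error 5.0%, whatever δ is.

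**2:2:1 in the last cohort (control the smallest).**
- Each intervention arm: 68/3 + 54 × 2/5 = 22.7 + 21.6 = 44.3; last-cohort share 21.6/44.3 = 48.8%.
- Control: 22.7 + 54 × 1/5 = 22.7 + 10.8 = 33.5; last-cohort share 10.8/33.5 = 32.3%.
- Difference in shares: 0.165. SE = √(1/44.3 + 1/33.5) = 0.229.

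| δ (SD) | Bias (SD) | z | Type I error |
|---|---|---|---|
| 0.3 | 0.165 × 0.3 = 0.050 | 0.216 | 0.0148 + 0.0406 = 5.5% |
| 0.5 | 0.165 × 0.5 = 0.083 | 0.361 | 0.0102 + 0.0549 = 6.5% |

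The two intervention arms have the same cohort mix here, so their comparison with each other is unbiased. It would be affected only if the ratio between those two arms also changed.

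**Sensitivity to cohort sizes.** With 41, 41 and 40 and the same 2:2:1 in the last cohort, δ of 0.2 to 0.5 SD gives a bias of 0.03 to 0.07 SD and a type I error of 5.2% to 6.1%.

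**With a cohort term.** A within-cohort comparison removes any cohort effect shared by all arms, so the bias above becomes 0. In the 34/34/54 case the SE rises from 0.229 to 0.232; in the 41/41/40 case, from 0.227 to 0.229.

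**The case against.** Four objections carry weight.

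1. **The risk is conditional.** Both statements say that ratios might be changed, and the article reports no change. This stands: the article does not show that the arms are already confounded with calendar period.

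2. **The covariate lists are open.** They are introduced as examples, this is a condensed article, and an analysis plan that is not shown may include cohort. This also stands, so it would be wrong to say that the analysis excludes a cohort term. What remains is that the article itself grants the ratio change and describes the model without tying the two together.

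3. **The effect is small for a modest change.** It is: about half to one and a half percentage points of type I error. A reader could get 0.27 SD by supposing a last cohort with no controls (share 27.0/49.7 = 54.4% against 0%, times 0.5). The arithmetic is right, but no section proposes such a cohort, and participants are said to be allocated among three arms. That figure is not a fair measure of this plan.

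4. **Session changes between cohorts are a different matter.** The order or spacing of sessions may be revised after each cohort, but this reaches only the intervention arms. It is variation in the intervention, which an additive cohort term would not remove, and it is not part of the bias calculated here.

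A reader might also infer from the weekly meetings that ratios could be changed with sight of outcomes. The article does not support that. It ties ratio changes to recruitment and timing, and the sentence on monitoring outcomes mentions no data by arm. That sentence and the promise to keep outcome data blinded are loosely worded against each other and need reconciling, but they are not shown to conflict.

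**Conclusion.** The point holds as a conditional one. The article permits ratio changes in a trial enrolled by cohort, the stated trigger appears to have been met, and the described model does not commit to a cohort term. If a ratio changes and cohorts differ in outcome change, the comparisons with control are biased by about 0.05 to 0.08 SD, with a type I error of about 5.5% to 6.5%. These figures rest on the assumed cohort sizes, an initial 1:1:1, a 2:2:1 last cohort and a 0.3 to 0.5 SD difference in change. The bias is zero if the ratio stays constant, and larger only if a cohort lacks an arm. Severity: should be fixed. Confidence: moderate, because no ratio change is reported and the covariate lists leave room for cohort.

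**What to change.** - Randomize within cohort. Allow a ratio change only between cohorts, fixed before the first randomization of the new cohort, on recruitment counts alone, with all three arms open in every cohort.
- Include cohort and cohort-by-time as fixed terms in every between-arm model. The interaction is needed because the bias lies in change over time; a cohort main effect alone does not address it.
- Report arm counts per cohort and the ratio used in each.
- Separately, reconcile the statement on weekly monitoring with the statement on blinding by saying that those meetings see no outcome data by arm.

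The cost is a few sentences, some degrees of freedom (with three cohorts and four assessments, 2 for cohort and 2 × 3 = 6 for cohort-by-time), a very small rise in standard error under a modest ratio change, and slightly less freedom to fill the intervention groups. The rule is best written before the remaining participants are randomized.
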